## **6.5 Blood sampling during study**

During preliminary check-up one fasting blood sample (participant should not eat at least 3h before) for the analysis of routine laboratory parameters: Blood cell count, creatinine, glucose, CRP, bilirubin, GOT, GPT,  $\gamma$ GT. Another 10ml of blood is taken for genotyping and 30ml for RNA and protein extraction. In total 60ml blood is taken during preliminary check-up.

During study day blood samples will be taken over 10 h for the analysis of EGCG kinetics and in addition 30ml blood is taken after 2h for RNA and protein extraction and the analysis of CRP. For the pharmacokinetic analysis following scheme is planned: blood sampling (each 10ml, EDTA monovette) at time point 0 (before intake of capsule, predosage) and 30min, 1,2,3,4,5,6,8 and 10 h after intake. The exact time of blood sampling is documented in the case report form (CRF) in the case that real time point differs more than  $\pm 5$  minutes (for 30 min sampling  $\pm 2$  minutes) from the planned time point. Exact time points will be used for pharmacokinetic calculations. In total 120ml blood is taken during study day.

## **6.6. Experimental Procedure**

### **6.6.1 Genotyping**

Blood sample for genotyping are frozen at  $-20^{\circ}\text{C}$  within 24h after sampling. For DNA extraction blood samples are slowly defrosted at room temperature. DNA is extracted with standardized procedure (Qiagen DNA extraction kit). For genotyping validated methods are used (DNA-sequencing, Taqman, PCR-RFLP)

### **6.6.2 Genome-wide analysis**

This study is not primarily designed for the analysis of genome-wide DNA-data. But it is possible under certain conditions (for example that the kinetic results strongly differ in 6 out of 100 participants) that a genome-wide analysis could make sense. Therefore participants were asked to consent in a genome-wide analysis. These analyses have only the aim to explain the nutrikinetic or effects of EGCG. (narrow definition of the aim)

### **6.6.3 Candidate gene analysis**

Variants in genes, which probably influence nutrikinetic or the effect of EGCG according to literature or could at least be involved due to biological plausibility, are analyzed. In a first step we will analyze known functional variants as well as gene variants with common alleles or haplotypes. We will analyze genes like Catechol-O-Methyltransferase (COMT), OATP1A2, -1B3 and other relevant transport proteins. Further we will analyze genes coding for glucuronyltransferases, and if we see significant effects of EGCG on oxidative stress, inflammation or cardio-vascular parameters we may also analyze genes related to this effects.

To identify new polymorphisms in genes which are yet not well characterized like OATP1B3 we plan to systematically sequence the coding and bordering non-coding regions of the gene

including 5'- und 3'-regions in a sub population of our participants. If we can detect such mutations we will establish specific genotyping assays.

#### **6.6.4 RNA-isolation and gene expression analysis**

Total RNA is isolated from blood sample using standard methods (Ficoll cell separation, Qiagen RNeasy Mini Kit, Pax-Gen). It is planned to investigate if the expression of genes of the drug transport, metabolism, cell growth, generation or detoxification of reactive oxygen species is changed by a 4-day treatment with EGCG. Expression of candidate genes is quantified using qPCR (Sybr Green, TaqMan). In this respect, as for the genetic analysis, participants were asked to consent in a genome-wide analysis. In this case common Affymetrix Expressions-Microarrays should be used. In addition to RNA, gene expression differences will also be semi-quantitatively on protein level using western blot. For this reason protein fractions are isolated from isolated lymphocytes and frozen at -80°C.

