### **8.6 Eating and drinking during study.**

One day before the study day participants should not drink tea, especially green tea. A list containing information about food which could contain EGCG or similar compounds is given to the participants ahead of study.

Participants must not eat from 22:00 the day before the study day until two hours after the intake of the study drug at study day. Afterward the participants get a bread roll, lunch and dinner during their stay on the research ward at study day. For the choice of the dish, attention will be payed that the food does not contain EGCG or similar substances. For drink participants get mineral water.

Because it is known that nutrikinetic of EGCG is influenced by food intake (more than 3-times higher blood levels under fastened then fed conditions) participants should not eat additional food. No more than 3L of water is allowed to be drunk during study day

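### The before and after samples for gene expression are not taken under matched conditions, so a change cannot be assigned to the 4-day EGCG course alone

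*Protocol*

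**What the plan says.** Section 6.6.4 asks whether expression of several gene groups, ending with genes for "detoxification of reactive oxygen species is changed by a 4-day treatment with EGCG", and plans qPCR on RNA and western blots on protein from lymphocytes. Section 7.3 lists expression changes among the secondary outcomes. The Summary describes an open study, and no untreated or placebo group is planned.

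The samples are set in sections 6.4 and 6.5.

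- **Before.** At the preliminary check-up, 6.5 asks for "one fasting blood sample (participant should not eat at least 3h before" the visit) for routine laboratory tests, and then says "Another 10ml of blood is taken for genotyping and 30ml for RNA and protein extraction". The food rule is written for the routine sample; the RNA and protein sample is covered only because it is drawn at the same visit. No clock time is given, and the schema in 6.4 places the visit at day -x.
- **After.** On the study day, "in addition 30ml blood is taken after 2h for RNA and protein extraction and the analysis of CRP". The schema shows this as BE-3 (40 ml). Section 8.6 adds: "Participants must not eat from 22:00 the day before the study day until two hours after the intake of the study drug". Section 6.3 has one 150 mg capsule taken at time 0, after four days of two capsules a day at home.

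**The concern.** With no control group, a before/after difference can be credited to the treatment only as far as the two samples are alike in everything else. Here they may differ in hours without food and in time of day, and they always differ by one further capsule taken 2 h before the second sample. Genes of metabolism, transport and oxidative stress in blood cells could plausibly respond to any of these.

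At stake is the interpretation of a secondary outcome. A change attributed to four days of EGCG might be an acute response to a single fasted dose, or a feeding or time-of-day effect. Later analysis cannot repair this, because the study day has no pre-dose RNA sample and the follow-up check-up in 6.7 is not stated to include one.

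**Working it through.** The protocol gives no sample size, test or power for this comparison, so there is no planned figure to reproduce. The check sets the two sampling conditions side by side.

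| Condition | Before (check-up) | After (study day, BE-3) |
|---|---|---|
| Capsules taken so far | 0 | 4 × 2 + 1 = 9 |
| Time since last capsule | none taken | 2 h |
| Time without food | 3 h or more (6.5) | since 22:00 (8.6) |
| Clock time | not fixed | morning |
| Interval to first dose | not fixed (-x in 6.4) | not applicable |

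**Hours without food at the after sample.** Hours = 2 (22:00 to midnight) + clock hour of the dose + 2 (to BE-3). The dose time is not stated, so it is assumed:

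- 07:00: 2 + 7 + 2 = 11 h
- 08:00: 2 + 8 + 2 = 12 h
- 09:00: 2 + 9 + 2 = 13 h

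The baseline minimum is 3 h. The schema's footnote allows glucose or a soft drink for hypoglycemia before BE-3, so a few after samples may not be fully fasted either. Sections 6.3 and 6.4/8.6 disagree on when food is first given after the capsule and must be reconciled, but the 2 h sample precedes food under either version.

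**The extra capsule.** The 4-day course is 4 × 2 = 8 capsules, and the after sample follows a ninth. Section 2.2 puts the peak at 1 to 2 h, so a 2 h draw falls at the edge of that window. The eight home capsules are taken with a meal (6.3), while the ninth is taken fasting. Section 8.6 says fasted blood levels are more than three times the fed ones. On the protocol's own figures, the after sample thus reflects an acute exposure higher than that from any single dose in the course being evaluated.

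**What a pre-dose draw would contain.** Assume 12 h since the last evening capsule and simple exponential decline. The fraction of that dose's concentration remaining is 0.5^(12/half-life), with the half-life of 2 to 4 h from section 2.2:

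- 2 h: 0.5^6 = 1.6%
- 3 h: 0.5^4 = 6.25%
- 4 h: 0.5^3 = 12.5%

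A sample at BE-0 would therefore be largely free of acute drug. It would reflect what the 4-day course leaves behind, not expression at peak exposure.

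**The case against.** The best defence is that the 2 h draw may be sensible. EGCG is short-lived and is said not to accumulate, so sampling near the peak during continuing intake is a reasonable way to look for an on-treatment effect, and a pre-dose draw might miss it. The outcome is secondary, and section 7.5 calls the study exploratory and pilot-like. Matching the fast would not cure an uncontrolled design, since visit and interval effects would remain. All of this stands. It means that moving the draw is a choice and not a correction. It does not explain why 6.6.4 names the 4-day treatment alone, or why the baseline fast is left loose. Exploratory status bears on multiplicity, not on what a difference means.

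A reader might infer more than the protocol supports:

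- *All 100 pairs are shifted in one direction.* This holds for the extra capsule only. Three hours is a minimum, so some participants may arrive fasted overnight, and a clock-time effect has no stated direction.
- *A modest artefact would be declared an EGCG effect, because 100 pairs detect (1.96 + 0.84)/√100 = 0.28 within-pair SD with 80% power.* That is the generic detectable shift for 100 pairs. It does not measure bias, and the protocol gives no figure for how feeding or time of day moves these genes.
- *CRP and the epigenetic outcome fail in the same way.* No before/after CRP comparison is stated. CRP appears at both visits in 6.5 but not in the check-up list in 6.1. The point about DNA applies only if the two DNA samples are compared for epigenetic change.
- *A false signal would contaminate the genetic analysis.* Section 6.6.3 only permits further genes to be analysed if effects are seen, and does not tie this to the RNA pair. Genotype does not change with fasting.

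**Conclusion.** The concern holds for the before/after comparison of RNA and western-blot protein. In every participant the study-day sample combines the 4-day course with an acute fasted dose taken 2 h earlier, and the two cannot be separated. Fasting is also unmatched: a 3 h minimum against about 11 to 13 h, if dosing is at 07:00 to 09:00. Clock time is uncontrolled at baseline. These two conditions need not differ in every participant, and the resulting bias cannot be quantified from the protocol. The primary comparison of oral clearance by genotype does not use this sample pair and is unaffected.

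**What to change.** 1. In 6.4 and 6.5, require the check-up RNA and protein sample to be drawn after the same overnight fast as on the study day (no food from 22:00) and in the same morning clock window as the study-day sample. The cost is that check-ups become fasting morning visits; no extra blood or visit is needed.
2. Reconcile 6.6.4 with 6.5. If the 2 h draw is kept, describe the estimated effect as that of 4-day intake plus an acute fasted dose, from an uncontrolled before/after comparison. This is a wording change.
3. If the effect of the 4-day course alone is wanted, drawing the same 30 ml at BE-0 is an option. The venous line and a blood draw are already planned then, so the total volume is unchanged. The price is the near-peak signal, and the investigators should make that choice openly.
4. If CRP or DNA from the two visits is to be compared, say so, apply the same matching, and reconcile the check-up lists in 6.1 and 6.5.

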#### **6.6.5. Bioanalytics**

For the determination of EGCG concentration in the blood, 10ml EDTA blood samples are collected, protected from light and centrifuged within 30min after collection for 10 min and 2000g at room temperature. The supernatant (plasma) is divided into 500µl aliquots and 500µl stabilization buffer is added. Stabilization buffer contains EDTA and ascorbic acid. [100 mg ethylenediamin-tetraacidic acid (EDTA) disodiumsalt and 10 g ascorbic acid solved in 1000 mL sodium acetate buffer (35 mM: 2.38 g sodium acetate trihydrate and 1.00 mL acetic acid dissolved in water and adjusted to 1000 mL)]. Stabilized plasma samples are stored at -80°C and later shipped on try ice.

The analytic measurements will be carried out using HPLC and electro-chemical detection at the department of clinical pharmacology at the university Göttingen (director: [name]. med. [name]) [13]. It is planned to analyze plasma concentrations of EGCG as the major aim of the project. If possible the plasma concentration of methylated metabolites (COMT), as well as glucuronides and sulfate metabolites of EGCG should be determined in the plasma samples or urine in order to characterize the causes of this variability.

#### **6.7. Allowance and follow-up**

Follow-up includes a check-up similar to the Preliminary check-up and performed after the study day. Participants get an allowance of 80€.

## **7. Statistical analysis**

### **7.1. General**

It is the aim of this study to investigate in vivo the influence of genetic polymorphisms in COMT, OATP1A2, OATP1B3 and further molecules involved in EGCG effect on the kinetics of EGCG. It should be tested if plasma-concentration-time profiles (AUC, Cmax, and oral clearance) differ in relation to the genotype.

## **7.2 Primary outcome**

Oral clearance (Dosage/AUC) of 150mg EGCG in carriers of genetic polymorphisms compared to wild type carriers.

## **7.3 Secondary outcome**

Maxima blood concentration (Cmax), Time of the maximal blood concentration (Tmax), half life time (T1/2), adverse events, changes in gene expression profiles, epigenetic changes in blood cells, concentration profile of the used capsules including description of rate and variability of absorption, distribution (alpha half-life) and terminal elimination (beta half-life) of the relevant green tea catechins as far as they are detectable.

## **7.4 Sample size estimation**

With a sample size of n=100 it is possible to detect genetic variation with an allele frequency of 5% at least once with a level of significance of 5%.

Assuming a frequency of 20% of carriers of the methionine variant (heterozygote plus homozygote carrier) and an allele frequency of 11% for the COMT polymorphism an effect on the pharmacokinetics would be detectable in n=100 participants. It had been shown that a mean AUC of 1403 ng/ml h with a standard deviation of 632 can be detected after multiple dosing of 200mg EGCG in n=9 participants [8]. If n=20 participants carry either Val/Met or Met/Met genotypes and n=80 carry Val/Val genotype a difference of 30% and more in the oral clearance of EGCG could be detected with a power of 80% and a significance of 0.05 (sample size calculated with nQuery Advisor 4.0).

In addition, with the estimated sample size of n=100 it is possible to determine the distribution of nutrikinetic parameters of EGCG in healthy participants and give evidence if there are sub-populations showing a poor absorption or fast metabolism or a good absorption and a poor elimination of this substances.

## **7.5 Statistical methods:**

The results will be analyzed using non-parametric Jonckheere Terpstra Trend Tests based on the estimation of a trend in the EGCG kinetics in carriers of wild type > heterozygote > homozygote.

Wild type and homozygote carriers will be compared with parametric t-test. This study is of exploratory nature. A significant association detected by testing individual factors is suggested to be important, even if it is no longer significant after adjusting to multiple testing. This study is to our knowledge the first trial studying the genetic variability of green tea catechin EGCG and has the characteristics of a pilot study.

AUCs will be calculated using non-compartmental analysis as well as population kinetic modeling. An experimental analysis with calculation of median, mean, variance and graphic presentation in Box-Plots will be conducted.

Participants discontinuing the study or fulfilling exclusion criteria will be marked as drop-out and will be excluded from nutrikinetic analysis.

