### 2.3 Genetic polymorphisms in COMT, OATP1A2 and 1B3

Intestinal and hepatic influx transporter, as well as the (mainly hepatic) efflux transporter of EGCG and transporter and enzymes involved in biotransformation show genetic variability. Catecholamin-O-transferase (COMT) is an enzyme expressed in liver, kidney and brain and is involved in the methylation of neurotransmitters and xenobiotics. EGCG is methylated via COMT. This could in principle explain the interesting effect on the catecholamine metabolism (most probably outside the brain). A genetic polymorphism is described resulting in an amino acid exchange from valine to methionine. This change results in a trimodal distribution of enzyme activity with high activity in carriers with Val/Val form, medium activity in carriers with Val/Met and low activity in carriers of the Met/Met genotype. [10].

Many genetic variants are described in OATP1A2 and 1B3 transporter, but is not yet studied to which extent these variants effect the transport of EGCG.

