### **4.2. Inclusion criteria**

- Healthy male and female participants after physical check up
- German or northern European origin (to obtain a genetic homogenous population, no intention to racism)
- Written informed consent
- Age > 18 years
- BMI between 18 and 30

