### **4.3. Exclusion criteria**

- For female pregnancy and breast feeding
- Acute and chronic disease
- Each acute infectious disease (start of the participation can be delayed)
- Regular drug intake with exception to oral contraceptives
- Need to take drugs during study period and especially at study day (e.g. analgesics or antibiotics).

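### Section 7.5 names only unadjusted genotype tests and writes one trend order for every kinetic measure; a two-sided, covariate-adjusted regression of log oral clearance on carrier status would fit the primary outcome better

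*Protocol*

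**What the plan says.** Protocol section 7.2 defines the primary outcome as "Oral clearance (Dosage/AUC) of 150mg EGCG in carriers of genetic polymorphisms compared to wild type carriers". Section 7.4 sizes the trial for that contrast: 20 carriers of the COMT methionine variant against 80 Val/Val participants, a 30% difference in oral clearance, 80% power and a significance level of 0.05.

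Section 7.5 names two tests:

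- "The results will be analyzed using non-parametric Jonckheere Terpstra Trend Tests", built on "a trend in the EGCG kinetics in carriers of wild type > heterozygote > homozygote".
- As the second test, a comparison of two genotype groups only: "Wild type and homozygote carriers will be compared with parametric t-test".

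No covariate, transformation or sidedness is given for either. The same section says "AUCs will be calculated using non-compartmental analysis as well as population kinetic modeling", and calls the study exploratory with the character of a pilot.

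On the participants, section 4.2 admits both sexes, adults without an upper age limit and "BMI between 18 and 30". Section 4.3 excludes "Regular drug intake with exception to oral contraceptives". Section 10.1 lists age and gender among the personal data that may leave the test facility. On direction, section 2.3 describes graded enzyme activity for COMT, but says of the OATP1A2 and OATP1B3 variants that it "is not yet studied to which extent these variants effect the transport of EGCG".

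**The concern.** Three features of section 7.5 fit the primary outcome poorly.

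1. **No adjustment is possible with the named tests.** A Jonckheere-Terpstra test and a two-sample t-test take no covariates. Any variation in clearance due to sex, age or body size stays in the error term, and an imbalance in the small carrier group cannot be taken into account in the estimate.
2. **Contrast and scale.** The primary outcome and the sample size compare all carriers with wild type, but the t-test compares only homozygotes with wild type. Its scale is not stated. On the raw scale, a t-test of clearance and one of its reciprocal, AUC, need not agree. On the log scale they differ only in sign.
3. **Direction.** One order is written for kinetics in general, while section 7.1 wants AUC, Cmax and oral clearance compared by genotype. With clearance equal to dose over AUC at a fixed 150 mg, a descending order in one is an ascending order in the other. For the transporters the protocol itself has no direction to offer.

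At stake are precision and, if the trend test were run one-sided, the ability to see variants that act against the written order.

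**Working it through.** **Inputs.** From section 7.4: AUC mean 1403 and SD 632; 20 carriers and 80 wild type; 30% difference; power 80%; alpha 0.05; allele frequency 11%. Not in the documents: the share R² of the variance of log clearance that sex, age and body size explain. This is an assumption, shown from 0 to 0.30.

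**Spread.** CV = 632/1403 = 0.4505. For a lognormal variable, log SD = √ln(1 + 0.4505²) = 0.4298. Log clearance and log AUC have the same SD at a fixed dose.

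**The plan's own 80%.** Standard error factor √(1/20 + 1/80) = 0.25. Noncentrality = difference / (SD × 0.25), with 98 degrees of freedom.

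| Scale and effect | Noncentrality | Two-sided power | One-sided power |
|---|---|---|---|
| Raw, 0.30 / (0.4505 × 0.25) | 2.664 | 75.1% | 84.1% |
| Log, ratio 1.3: 0.2624 / (0.4298 × 0.25) | 2.442 | 67.6% | 78.2% |
| Log, ratio 0.7: 0.3567 / (0.4298 × 0.25) | 3.319 | 90.8% | 95.1% |

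The stated 80% lies within two points only of the one-sided log calculation at ratio 1.3. That is weak evidence on how it was obtained and does not settle sidedness.

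**Gain from adjustment.** Multiply the variance by (1 − R²); the equivalent sample size is 100/(1 − R²). Two-sided, log scale, 20 v 80, before any charge for the covariates' degrees of freedom:

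| Assumed R² | Power, ratio 1.3 | Power, ratio 0.7 | Equivalent N |
|---|---|---|---|
| 0 | 67.6% | 90.8% | 100 |
| 0.05 | 69.9% | 92.1% | 105 |
| 0.10 | 72.2% | 93.4% | 111 |
| 0.20 | 77.1% | 95.7% | 125 |
| 0.30 | 82.4% | 97.5% | 143 |

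**Cost of adjustment.** With four covariates the variance is inflated by about 97/93 = 1.043, so the break-even R² is 1 − 93/97 = 0.04. A simulation (4000 runs, lognormal, genotypes 80/19/1, four covariates, ratio 0.7) gave adjusted power of 89.6%, 92.0%, 94.9% and 97.3% at R² of 0, 0.10, 0.20 and 0.30, against about 90–91% unadjusted.

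**Scale.** In the same simulation at ratio 0.7 and R² = 0, two-sided power for carriers v wild type was 85.6% for a raw t-test, 90.8% for a log t-test and 88.9% for Jonckheere-Terpstra. The log scale gains about 5 points over a raw t-test but only about 2 over the rank test, which does not change under a log transformation.

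**Direction.** At ratio 0.7, taken as the written direction for clearance, Jonckheere-Terpstra had 94% power one-sided and 89% two-sided. For the mirror-image effect (ratio 1/0.7 = 1.43) the one-sided test had about 0% and the two-sided test about 89%.

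**Contrast.** At an allele frequency of 11% under Hardy-Weinberg, 100 participants give 100 × 0.89² = 79.2 wild type, 100 × 2 × 0.11 × 0.89 = 19.6 heterozygotes and 100 × 0.11² = 1.2 homozygotes. The chance of fewer than two homozygotes is about 66%. Section 6.1 allows selection of wanted genotypes, so the actual mix may differ.

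**The case against.** The strongest reply is that most of this is silence rather than error. Covariates, transformation and sidedness are commonly settled in a statistical analysis plan, which is not shown. The study calls itself exploratory, and unadjusted rank tests are valid for that purpose. Chance imbalance is already covered by the error rate of a valid unadjusted test, so adjustment is a matter of precision and not of bias. Population kinetic modelling is planned and could carry covariates.

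Much of this stands, and it rules out four stronger readings that a reader might infer:

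- *That the trend test is one-sided and so blind to opposite effects.* Jonckheere-Terpstra needs an order of the groups, and the protocol supplies one. Run two-sided, it gives the same p-value with the order reversed. No section states one-sided testing, so the 0% figure is conditional.
- *That the analysis is on raw clearance.* The scale is simply not stated. The point touches only the t-test.
- *That contraceptive use is already on file.* Section 4.3 only permits it; no section says it is recorded for analysis.
- *That adjustment is free.* At R² near zero it loses about a point.

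What does not stand is that the analysis plan can simply fill the gap. Section 7.5 names specific tests that cannot take covariates, so adjusting would mean departing from them. The modelling is named there for calculating AUCs, not for testing genotype.

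**Conclusion.** The concern holds as a worthwhile improvement, not as an invalid analysis. The protocol commits to unadjusted tests although age, gender and body size are available, its t-test does not match the carrier contrast that was defined and sized, and its single trend order cannot describe clearance and AUC together.

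The size depends on an R² that the documents do not give and on a direction of effect that they do not state. For an R² of 0.05 to 0.30 the gain is about 2 to 15 points of power at ratio 1.3 and about 1 to 7 points at ratio 0.7, where power already exceeds 90% unadjusted. Below an R² of about 0.04, adjustment with four covariates does not pay. The calculations also assume lognormal clearance with the cited spread and 20 v 80 participants. The matter of direction costs power only if the trend test is run one-sided. Adjustment does not cure the shortage of homozygotes; the carrier term avoids depending on them.

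**What to change.** Reword section 7.5 so that:

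- The primary analysis is a linear regression of log oral clearance on a carrier indicator (carriers v wild type), with sex, age and body weight or BMI as prespecified covariates. Add oral contraceptive use only if it is recorded.
- An allele-count term in the same model serves as the trend analysis.
- All tests are stated to be two-sided, and effects are reported as geometric mean ratios with 95% confidence intervals.
- A two-sided Jonckheere-Terpstra test is kept as a sensitivity analysis.

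This takes a few lines of text. Age and gender are collected and body size is implied by the eligibility check, so no new measurement is needed; contraceptive use would need confirming on the case report form. The statistical cost is three or four degrees of freedom, about one point of power if the covariates explain almost nothing, and about five points in the written direction if a one-sided test had been intended.

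### The t-test in Protocol section 7.5 (wild type against homozygotes) is not the carrier against wild type contrast that sections 7.2 and 7.4 name and power, and for COMT it is close to empty

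*Protocol*

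**What the plan says.** Three parts of the Protocol bear on the comparison.

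- **Section 7.2 (primary outcome):** "Oral clearance (Dosage/AUC) of 150mg EGCG in carriers of genetic polymorphisms compared to wild type carriers". The contrast is carriers against wild type.
- **Section 7.4 (sample size):** The worked case is COMT, with 20% carriers and "an allele frequency of 11% for the COMT polymorphism". The power statement pools the two carrier genotypes: "If n=20 participants carry either Val/Met or Met/Met genotypes and n=80 carry Val/Val genotype a difference of 30% and more" is said to be detectable with 80% power at a significance level of 0.05. Variability comes from "a mean AUC of 1403 ng/ml h with a standard deviation of 632", observed in nine participants of a cited multiple-dose study.
- **Section 7.5 (methods):** Two tests are named. The first is a Jonckheere-Terpstra trend test over wild type, heterozygotes and homozygotes. The second is the t-test: "Wild type and homozygote carriers will be compared with parametric t-test". The section also plans descriptive means, medians, variances and box plots, and calls the study exploratory, with the character of a pilot.

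No two-group test of pooled carriers against wild type is named, and section 7.5 does not say which of its two tests decides the primary outcome.

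**The concern.** The sample size rests on a two-group comparison in which heterozygotes supply nearly all of the smaller group. The two-group test in section 7.5 removes those heterozygotes. For COMT, the only gene for which power is claimed, that leaves about one person in the smaller group.

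Three things are at stake:

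- The 80% power statement describes a test that section 7.5 does not list.
- The listed t-test will often be impossible. Otherwise it will usually turn on one to three people. Section 7.5 treats a nominally significant single-factor result as important even if it does not survive multiplicity adjustment, so a result driven by one Met/Met participant could be reported as an association.
- Section 7.4 expresses the effect as a percentage difference in clearance between carriers and wild type, but section 7.5 names no estimate of that difference.

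**Working it through.** **Inputs, all from Protocol section 7.4.** Allele frequency q = 0.11; groups 20 and 80; mean AUC 1403 and SD 632 ng/ml h; difference 30%; significance 0.05. Sidedness and scale (raw or log) are not stated. I assume that the coefficient of variation of AUC carries over to oral clearance, and that genotypes follow Hardy-Weinberg proportions without selection.

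**1. The plan's own power figure.** The CV is 632/1403 = 0.450. The standardised difference is d = 0.30 × 1403/632 = 420.9/632 = 0.666. For two groups the noncentrality is d × √(n₁n₂/(n₁+n₂)). For 20 against 80 this is 0.666 × √16 = 2.66 on 98 degrees of freedom.

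| Reading of the 20 v 80 comparison | Power |
|---|---|
| Raw scale, two-sided | 75% |
| Raw scale, one-sided | 84% |
| Log scale, two-sided, ratio 1.3 | 68% |
| Log scale, two-sided, ratio 0.7 | 91% |
| Log scale, one-sided, ratio 1.3 | 78% |

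The stated 80% is not reproduced on the plain two-sided raw-scale reading. It lies within the range of readings that the text leaves open, so it is not shown to be wrong, and the present point does not depend on it.

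**2. Expected genotype counts per 100.**

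- Val/Val: 0.89² = 0.792, about 79
- Val/Met: 2 × 0.11 × 0.89 = 0.196, about 20
- Met/Met: 0.11² = 0.0121, about 1.2

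Carriers total 20.8 per 100, which agrees with the plan's 20%. Working back from exactly 20% carriers gives q = 0.106 and 1.1 homozygotes.

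**3. Chance of too few homozygotes.** With a Binomial(100, 0.0121) count:

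- none: 0.9879¹⁰⁰ = 0.296
- exactly one: 0.363
- none or one: 0.659

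With none, the t-test cannot be run. With one, the homozygote group has no variance of its own and the test relies entirely on the wild-type variance.

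**4. Power of the t-test as written** (30% difference, two-sided 5%, raw scale, noncentral t).

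| Groups | Noncentrality | Power |
|---|---|---|
| 1 v 79 | 0.666 × √(79/80) = 0.66 | 10% |
| 2 v 79 | 0.666 × √(158/81) = 0.93 | 15% |
| 3 v 79 | 0.666 × √(237/82) = 1.13 | 20% |
| 20 v 80 (powered contrast) | 2.66 | 75% |

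With one homozygote, the difference detectable with 80% power is about 129% of the mean; with two it is about 91%.

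**5. What the trend test recovers.** Power was simulated with 4,000 runs per scenario, an 80/19/1 split and a 30% shift in all carriers.

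| Data | Jonckheere-Terpstra | Pooled-carrier rank test |
|---|---|---|
| Normal | 73.2% | 73.4% |
| Log-normal, 30% lower | 88.2% | 88.3% |
| Log-normal, 30% higher | 65.0% | 65.3% |

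With about one homozygote, the trend test is in practice a rank test of carriers against wild type.

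**The case against.** The strongest reply is that section 7.5 lists the Jonckheere-Terpstra test first, as the means by which the results will be analysed, and that this test uses every carrier. Its power is within about one percentage point of a pooled-carrier rank test. This stands. A reader might infer from the t-test alone that the powered question is never tested, or that a null result would say nothing about COMT. The document supports neither: the trend test addresses the question, and a null result from it would be informative. Nor does section 7.5 call the t-test the primary analysis.

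Three further replies have some force.

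- **Genotype-selected entry.** Section 6.1 arranges the check-up for carriers of a wanted genotype, which could raise the number of homozygotes. No target number is given, however, and section 7.4 plans on 20 and 80. Selection therefore qualifies the 30% and 66% probabilities without removing the problem.
- **Other genes.** Sections 6.6.3 and 7.1 extend the analysis beyond COMT. If a variant had an allele frequency of 20%, about 4 of 100 would be homozygous; at 50%, about 25 (both assumed for illustration). The t-test may be usable there, so the near-empty result belongs to COMT as planned and not to every variant.
- **Exploratory status.** This lowers the stakes and explains the relaxed handling of multiplicity. It does not explain why the two-group test differs from the named primary contrast.

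The trend test does not close the gap completely. It gives a p-value but not the size of the carrier against wild type difference. The descriptive summaries do not name that contrast or an interval, and the sample size is not said to rest on the trend test.

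**Conclusion.** The mismatch is real and can be read directly from sections 7.2, 7.4 and 7.5: the contrast that is named and powered is not the one given to the t-test. For COMT, on the plan's own 11%, the t-test discards about 20 of 21 carriers, cannot be run in about 30% of samples, and has 10% to 20% power with one to three homozygotes, against 75% for 20 against 80. These figures assume Hardy-Weinberg proportions, no genotype enrichment, the AUC coefficient of variation applied to clearance, a two-sided test and the raw scale.

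The consequence is limited. The plan already contains a valid all-carrier test, and the study is declared exploratory. What is missing is agreement between the sample size and the listed tests, an estimate of the difference, and a statement of which test decides. This should be fixed, but the primary objective is not lost without it.

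**What to change.** In section 7.5:

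- Make the two-group comparison for COMT Val/Met plus Met/Met against Val/Val on oral clearance, with an estimate of the difference and its 95% confidence interval. Analysing log clearance and reporting a ratio is an option, not a requirement of this point.
- State whether this comparison or the trend test decides the primary outcome. If the trend test is chosen, base the sample size statement in section 7.4 on it.
- Keep the Jonckheere-Terpstra test.
- Label wild type against homozygote as descriptive, and run it only for variants that reach a minimum number of homozygotes fixed in advance (for example 5).
- In section 7.4, state the sidedness and scale of the power calculation so that the 80% can be checked.

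The cost is about one paragraph of wording, with no further participants, samples or measurements.
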